## Abstract

**Background:**

Hospitalisation and a seven-day injectable antibiotics course are recommended by the World Health Organization (WHO) to treat suspected clinical neonatal sepsis / possible serious bacterial infection (PSBI). Some infants presenting with PSBI signs associated with a moderate risk of mortality may only need a two-day hospitalisation followed by outpatient care treatment with oral antibiotics to complete seven days of antibiotics.

**Methods:**

A multi-centre, individually randomised, open-label trial will be conducted in seven sites in six countries: Bangladesh, Ethiopia, India (two sites), Nigeria, Pakistan and Tanzania. A common protocol will be used with the same study design, including the participants, intervention, comparison, outcomes, quality control, and analysis procedures. 0-59 days old infants presenting with moderate-mortality risk signs (low body temperature (<35.5°C), movement only when stimulated, stopped feeding well) or two or more signs of clinical severe infection (CSI) will be assessed and pre-enrolled. After 48 hours of hospital stay, clinically stable infants with a negative C-reactive protein test will be randomised either to hospital discharge on oral amoxicillin (intervention) or continued hospitalisation (control) arm. The intervention arm will receive oral amoxicillin for five days, whereas the control arm will receive injection gentamicin plus injection ampicillin for five more days plus supportive therapy if needed. We plan to enrol 5250 eligible young infants, 2625 infants in each of the two study arms. An experienced, well-trained independent outcome assessor will visit all enrolled cases on days 4, 8 and 15 after the initiation of treatment to assess the study outcomes in both intervention and control arms. The primary outcome of poor clinical outcome defined as death between randomisation and day 15 of initiation of treatment, deterioration during the 7-day treatment period, or persistence of the presenting sign of CSI at the end of the 7-day treatment period will be compared to assess if an early discharge and outpatient treatment leads to superior or at least non-inferior clinical outcome than continued inpatient treatment. The harmonisation of activities, including methods and processes, will be carried out diligently. Central training will be conducted by the WHO coordinating team, a central data coordination centre to collate all data, standardisation exercises for all clinical signs and internal and external monitoring. All the selected sites have extensive research experience. Through regular online and physical meetings, data-based monitoring, and physical site visits by WHO monitors, quality assurance and harmonisation will be ensured. This trial has been approved by the WHO and local site institutional ethics committees.

**Discussion:**

If the results show that young infants with moderate-mortality risk PSBI signs can be safely and effectively treated on an outpatient basis after a shorter hospital stay, it will reduce the burden on the hospitals, potentially reduce nosocomial hospital infections and increase access to treatment for families with poor access to health facilities. It may also reduce the health system costs (human and materials) and allow the overburdened hospitals to pay more attention to critically ill young infants. In addition, this evidence will contribute to making a case for reviewing the WHO PSBI guideline.

**Registration:**

International Standard Randomised Controlled Trial Number, ISRCTN16872570.

Around 2.3 million neonatal deaths occurred in 2021 worldwide, accounting for 47% of under-five deaths [1], even though this burden has decreased recently. In South Asia and sub-Saharan Africa, neonatal infections account for over 35% of all neonatal deaths [2]. The World Health Organization (WHO) integrated management of childhood illness (IMCI) algorithm classifies neonates and young infants with clinically suspected sepsis as “Possible Serious Bacterial Infection (PSBI)” based on the recognition of seven clinical signs – fast breathing (60 breaths or more / minute) in 0-6 days old babies, severe chest indrawing, high body temperature (≥38^°^C), low body temperature (<35.5^°^C), not able to feed at all or stopped feeding well, convulsions, and movement only when stimulated or no movement at all among infants 0-59 days old [3]. WHO recommends that young infants with PSBI should be hospitalised and treated with injectable antibiotics and supportive care [4]. However, when referral to a hospital is not feasible, the WHO guideline recommends the further classification of these infants into those who are critically ill and those who have a clinical severe infection (CSI) (**Box 1**) [5]. Infants with CSI can be managed on an outpatient basis with a simplified regimen of injectable gentamicin for two or seven days and oral amoxicillin for seven days [5] based on clinical trials from Africa [6,7] and Asia [8,9].

Box 1Sub-classification of children with signs of possible serious bacterial infection when a referral is not feasible [5].Critical illness• convulsions• not able to feed at all• no movement at allClinical Severe Infection
*Low-mortality risk signs*
• high body temperature (≥38°C*)• severe chest indrawing• fast breathing of ≥60 breaths per minute in <7 days old infants
*Moderate-mortality risk signs*
• low body temperature (<35.5°C*)• movement only when stimulated• not feeding well / stopped feeding well*Thresholds based on axillary temperature.

Several countries have adopted the WHO PSBI guideline [5]. The safety and effectiveness of simplified outpatient therapy for PSBI have been shown through implementation research in several countries in Africa and Asia when hospitalisation is not feasible [10-21]. In the first two months of life, 8-10% of infants can have an episode of PSBI, whereas only 25-50% of them may reach a hospital for treatment in low and middle-income countries (LMICs). However, hospitalisation has innate risks, e.g. multi-drug resistant nosocomial infection [22-25], so only those sick young infants with PSBI signs should be hospitalised who have a favourable benefit-risk ratio. Secondary analysis of African Neonatal Sepsis Trial (AFRINEST) data [6,7] showed that those young infants with movement only on stimulation, not feeding well or low body temperature (<35.5^°^C) have a much higher case fatality risk (CFR) of 3.2%, 4.0% and 11.0%, respectively than those with high body temperature (>38^°^C), severe chest indrawing, or fast breathing (>60 breaths per minute in 0-6 days old infants), who had a CFR of 0.8%, 0.9% and 2.0%, respectively [26]. Infants presenting with two or more signs of CSI also had a relatively moderate risk of mortality (CFR = 5.7%). As expected, signs of critical illness were associated with a very high risk of death (convulsions (11.3%), unable to feed at all (22.9%) and no movements at all (25.0%)) [26].

An important inference from these findings is that infants with moderate mortality risk signs of CSI (stop feeding well, movements only on stimulation, low body temperature), multiple signs of CSI, as well as those with a critical illness [26] are likely to benefit from hospitalisation. In contrast, young infants with low mortality risk signs of CSI (severe chest indrawing, temperature >38^°^C or fast breathing with >60 breaths per minute in 0-6 days old) may not need inpatient treatment in a hospital. Additionally, analysis of AFRINEST data by place of treatment showed that CFR was three times higher (6.5%) in hospitalised young infants compared to those treated on an outpatient basis (1.9%) when they refused referral for the same signs of CSI [26]. This could be because they were either sicker, received sub-standard care at the hospital, or developed a nosocomial infection.

Of all young infants with any sign of CSI who received outpatient treatment in the AFRINEST study, 1.3% died up to 15 days after the initiation of treatment. Of those who died, 39.7% died within the first 48 hours of treatment. Among those who survived and were assessed at 48 hours of treatment, three-quarters of infants (73.9%) had no signs of illness. Of these infants who recovered by 48 hours, 0.4% died between day three and day 15. In contrast, mortality between day three and day 15 was higher among infants who still had the presenting sign at 48 hours (0.7%) or those who deteriorated (presence of new CSI sign / critical illness sign) at 48 hours (8.0%) (secondary analysis, unpublished data).

In high-income settings, infants with clinical suspicion of sepsis are hospitalised, and parenteral antibiotics are initiated after taking samples for sepsis screening and blood culture. After 48 hours, if the laboratory tests are negative and the infant is clinically well, antibiotics are stopped, and the infants are discharged [27-29]. However, this is hardly ever done in the LMICs, where once started, the parenteral antibiotics are continued for 7-10 days. We need evidence of whether sick young infants with moderate-mortality risk can be discharged early from the hospital.

The primary objective of this trial is to measure the effect of early discharge on an oral amoxicillin treatment on poor clinical outcomes compared with inpatient treatment in young infants 0-59 days old with moderate-mortality risk or two or more signs of CSI. We hypothesise that the majority of infants who improve by 48 hours will need shorter hospitalisation.

## METHODS

### Research question

Among hospital-admitted young infants 0-59 days old with any moderate-mortality risk sign or two or more low-mortality risk signs who clinically improve 48 hours after initiation of treatment and have a negative C-reactive protein (CRP) (population), are discharged from the hospital on oral amoxicillin at home for the next five days (intervention), compared with continued hospital management for next five days (control), non-inferior in terms of poor clinical outcome (outcome)?

### Study design, setting and sites

This will be an individually randomised, two-arm, open-label trial. The study will be conducted in seven sites in six countries Bangladesh, Ethiopia, India (two sites), Nigeria, Pakistan and Tanzania (**Table 1**).

**Table 1 T1:** Details of the study sites*

Study site	Description
Bangladesh	The study will be conducted in four hospitals. Zakaiganj Upazila Health Complex (ZUHC), Zakiganj (primary / public), Sunamganj District Hospital (SDH), Sunamganj (secondary / public), Moulvibazar District Hospital (MDH), Moulovibazar (secondary / public), and Habiganj District Hospital (HDH), Habiganj (secondary / public) in Sylhet. ZUHC has six paediatric beds and one radiant warmer, SDH has 14 beds, one incubator and three warmers, MDH has 17 beds and 17 warmers, HDH has 11 beds and 11 warmers in their Neonatal Intensive Care Units (NICU) / Special Neonatal Care Units (SNCU) respectively. All are functional 24 hours a day. Except for ZUHC, all hospitals have trained paediatricians, but none have a neonatologist. Oxygen is available 24 hours a day through cylinders.
Ethiopia	The study will be conducted in five hospitals. One named Tirunesh Beijing Hospital (secondary / public) in Addis Ababa, and four in the Oromia region named Bishoftu Hospital (secondary / public), Adama Hospital (secondary / public), Batu Hospital (General Hospital), Asella Hospital, Asella (Referral Hospital). Tirunesh Beijing Hospital has 22 beds and 17 incubators / warmers, Bishoftu Hospital has 15 beds and 17 incubators / warmers, Adama Hospital has 53 beds and 11 incubators / warmers, Batu Hospital has 18 beds and two incubators / warmers and Asella Hospital 40 beds and eight incubators / warmers in their NICU/SNCU respectively. All are functional 24 hours a day. All hospitals have trained paediatricians, but none have a neonatologist. Oxygen is available 24 hours a day through cylinders.

### Participants

All patients (<2 months old at presentation) admitted to the study hospitals with any moderate-mortality risk signs or two or more signs of CSI will be assessed for eligibility for this study 48 hours after initiation of treatment and considered for inclusion in the study if: 1) clinically well on day 3 (defined as the absence of all signs of critical illness or CSI (**Box 1**)) and 2) negative C-reactive protein and 3) the family lives within a catchment area where a follow-up of up to day 15 can be accomplished. Infants will be excluded from the study if they have any one of the following: 1) weight <2 kg at the time of presentation (if age at screening is less than 10 days) or weight-for-age <-3z (if age at screening is ≥10 days), or 2) signs of critical illness on admission (no movement at all, unable to feed at all, or convulsions), or 3) the appearance of any moderate-mortality risk sign or multiple low-mortality risk signs in the first 24 hours of life, or 4) hospitalised for any illness in the previous two weeks, or 5) prior use of injectable antibiotics in the last two days for the same illness (except the dose given for pre-referral administration), or 6) previously included in this study or currently included in any other study, or 7) any other reason to stay in the hospital, as decided by the treating physician.

Enrolled young infants who develop or are diagnosed with any new non-infectious problems after initiating antibiotics, such as jaundice, cardiac problems, etc. will be managed according to the hospital guidelines. They will not be considered to have poor outcomes.

Since some signs of PSBI mimic other conditions such as perinatal asphyxia, transient tachypnoea etc. it was decided during the investigators and Technical Advisory Group (TAG) meeting in March 2020 that newborns presenting with any sign of CSI within 24 hours of birth will not be eligible.

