### Outcomes

The primary outcome is “poor clinical outcome” defined as 1) death between randomisation (day three of initiation of therapy) and day 15 of initiation of therapy, or 2) presence of any sign of critical illness (no movement at all, unable to feed at all, or convulsions) or any sign suggestive of another serious infection, e.g. meningitis, bone or joint infection, on day four and eight of initiation of therapy, or 3) presence of any sign of CSI on day eight of initiation of therapy.

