### Outcome assessment

Due to the nature of the treatment, the trial cannot be blinded. To reduce potential measurement bias, we will use Independent Outcome Assessors (IOA) who will not be associated with the treatment of the infant. The IOAs who will be the Outcome Assessment Team members will conduct outcome assessment visits using the designated days four, eight and 15 post-admission. In the hospital arm, the outcome visits on day four will be done in the hospital, while on days eight and 15, visits will be done at home (or in the hospital or where ever the infant may have moved to). In the outpatient arm, the outcome visits on days four, eight, and 15 will be done at home or where ever the infant may have moved to. If the infant is not able to be seen on the specified day, then a window of additional time will be allowed for outcome follow up, i.e. for day four visit, an additional 24 hours; for day eight and day 15 visits, an additional 48 hours. The outcome team will continue to visit the family during this time window to complete these visits.

Outcomes will only be ascertained by the IOAs per the criteria mentioned above under outcomes. A case will be considered to have a poor clinical outcome if it is confirmed by the IOA.

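### The Participants section exempts infants with a new non-infectious problem from the primary outcome, the Outcomes section counts death and listed signs whatever the cause, and no text says which prevails

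*Protocol article*

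**What the plan says.** Three places in the protocol article bear on what counts as a primary event.

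- **Participants.** The rule covers "Enrolled young infants who develop or are diagnosed with any new non-infectious problems after initiating antibiotics". Jaundice and cardiac problems are given as examples in an open-ended list. These infants are managed under hospital guidelines, and then: "They will not be considered to have poor outcomes". The subject of that sentence is the infants, not the diagnosis. The next paragraph acknowledges that signs of possible serious bacterial infection can resemble non-infectious conditions.
- **Outcomes.** The primary outcome has three components: "death between randomisation (day three of initiation of therapy) and day 15 of initiation of therapy"; on days four and eight, "presence of any sign of critical illness (no movement at all, unable to feed at all, or convulsions") or a sign of another serious infection; and "presence of any sign of CSI on day eight of initiation of therapy". Death and the listed clinical signs carry no restriction by cause, and the Participants rule is not mentioned.
- **Outcome assessment.** "Due to the nature of the treatment, the trial cannot be blinded". Independent outcome assessors who take no part in treatment are used, and "Outcomes will only be ascertained by the IOAs per the criteria mentioned above under outcomes".

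**The concern.** The first two texts give different answers for the same infant. One who has jaundice and is still not feeding well on day eight, or who dies with a cardiac diagnosis, is an event under Outcomes and not an event under a literal reading of Participants. These are two stated rules that conflict, not a detail left to a later document.

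Four features make the conflict matter if the Participants rule is ever used to remove events:

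- The label has no stated criteria.
- Much of the period in which it can be given falls after randomisation, when the arm is known. (The period opens at the first antibiotic dose. Problems found before randomisation should be balanced between arms.)
- Opportunity for diagnosis differs. Control infants remain in hospital, while intervention infants are at home with assessor visits on days 4, 8 and 15 and one hospital return on day five.
- The outcome signs are non-specific, so a competing non-infectious explanation will often be available.

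At stake is the count of primary events in a non-inferiority comparison, and in particular whether every death is counted.

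**Working it through.** **Inputs.** From the Sample size section: one-sided alpha 0.025, relative-risk margin 1.40, 10% loss, control incidence 5% to 10%. From the Abstract: 2625 infants per arm. Evaluable per arm: 2625 × 0.9 = 2362.5, taken as 2362. At 5% incidence the control arm has 0.05 × 2362 ≈ 118 events. The documents give no rate of non-infectious labelling, so every labelling share below is an assumption.

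**Plan's own figure.** Power = Φ(0.4p / √(2p(1−p)/n) − 1.96).

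- p = 0.05: 0.020 / 0.006342 = 3.154; Φ(1.194) = 88.4%. Table 3 gives 88.4%.
- p = 0.075: 0.030 / 0.007664 = 3.914; Φ(1.954) = 97.5%. Table 3 gives 97.5%.

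The planning basis is therefore reproduced at these two rates. The same formula gives 99.6% at 10%, where Table 3 prints 96.6%. That is a separate matter and nothing here relies on it.

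**How few events matter.** 95% limits for the risk ratio on the log scale, with SE = √(1/a − 1/n + 1/c − 1/n), a = home events, c = hospital events, n = 2362:

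| Home events | Hospital events | Risk ratio | Upper limit | Below 1.40? |
|---|---|---|---|---|
| 129 | 118 | 1.093 | 1.394 | yes |
| 130 | 118 | 1.102 | 1.404 | no |
| 135 | 118 | 1.144 | 1.455 | no |
| 124 | 118 | 1.051 | 1.343 | yes |
| 124 | 112 | 1.107 | 1.420 | no |

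- *Home events removed.* 135 v 118 fails. Relabel six home events and 129 v 118 passes.
- *Hospital events removed.* 124 v 118 passes. Relabel six hospital events and 124 v 112 fails.

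Closer observation of inpatients would be expected to produce the second pattern rather than the first.

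**Error rates under assumed shares.** Let the true risk ratio sit at the margin, with 5% control incidence (about 118 v 165 events). The chance of declaring non-inferiority is Φ(ln(1.40 / RR_obs) / SE − 1.96), where RR_obs is the ratio after removal.

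- No removal: 2.5%.
- 5% of home events removed, no hospital events: RR_obs 1.33, SE 0.1183; Φ(0.434 − 1.960) = 6.3%.
- 10% of home events (about 17), no hospital events: RR_obs 1.26, SE 0.1198; Φ(0.880 − 1.960) = 14.0%.
- 10% of hospital events, no home events: RR_obs 1.556; 0.2%. If the arms are in truth equal, the same removal cuts power from 88.4% to 55.6% (difference scale, margin 1.40 times the observed control rate).
- 20% removed in each arm: RR_obs stays 1.40 and alpha stays 2.5%. Power falls from 88.4% to 80.1% (the formula above with p = 0.04: 0.016 / 0.005702 = 2.806; Φ(0.846)).

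**Deaths.** The Background reports 0.4% mortality between days three and 15 among infants recovered by 48 hours in an earlier outpatient study. If that applied here, 0.004 × 2362 ≈ 9 deaths per arm would be expected, so excluding even a few would visibly change the mortality component.

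**The case against.** A reader might infer that the protocol lets unblinded treating staff override all-cause death and strike events from the endpoint. The documents do not support that. The Outcome assessment section makes assessors who are independent of treatment the only source of outcome status, and directs them to criteria that contain no exclusion by cause. Nothing says that treating staff assign the label for outcome purposes, and nothing gives the Participants sentence precedence. The sentence follows a clause on routine management, and its natural sense is that newly found jaundice or a cardiac problem is not, on its own, treatment failure. The Data analysis section also describes poor clinical outcomes as including deaths. This objection stands against the strong reading.

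A reader might also infer a bias towards non-inferiority. That does not follow: the most plausible mechanism, closer inpatient observation, would remove control events and push towards a false failure.

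A third objection is that counting every event has its own cost. Non-infectious events common to both arms pull a risk ratio towards 1. For example, 12 added to each of 165 and 118 turn 1.40 into 177/130 = 1.36. That is a legitimate motive for some non-infectious provision.

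Finally, the article condenses a fuller protocol and refers to a Manual of Operations, so the absence of diagnostic criteria is not in itself a fault.

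What remains is the conflict. The printed sentence exempts the infant without exception, the assessors are not described as blinded to arm, and no text settles which rule governs across seven sites.

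**Conclusion.** The concern holds as an unresolved contradiction in the primary outcome definition, not as a stated rule that deaths are excluded. Its consequence depends on whether the Participants sentence is ever used to remove events, how often, and in which arm; the documents answer none of these. The direction of bias is therefore unknown. For scale only: at 5% incidence with 2362 evaluable per arm, about six reclassified events in one arm can change a borderline conclusion either way. Those examples were placed near the threshold, at the lowest planned incidence. No sample size, alpha, margin or power figure in the plan rests on the sentence. It should be fixed, because it touches whether deaths count and is easily settled before analysis.

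**What to change.** Reconcile Participants with Outcomes by replacing the sentence with wording such as: *A new non-infectious diagnosis is not in itself a poor clinical outcome; death, and any sign listed under Outcomes that the independent outcome assessor confirms, count regardless of presumed cause.* Carry the same rule into the assessor instructions. If a cause-attributed endpoint is wanted, report it as a sensitivity analysis only, ideally with cause judged without knowledge of arm.

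The cost is one sentence, with no change to sample size, margin or patient care. The downside is the slight dilution of the risk ratio towards 1 by non-infectious events common to both arms, which the sensitivity analysis would show.
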